**________________________________________________________**

### Principal Investigator: [name] [name], Lecturer (Occupational Therapy), PDUNIPPD

1. **Title:** Task-based and Magnified Mirror Therapy for Unilateral Spatial Neglect among Post-Stroke Subjects: A Randomized Controlled Trial
2. **Summary:**

Background: Up to 90% of the post-stroke survivors may experience the Unilateral Spatial Neglect (USN). USN is a deficit of attention and is described as the inability to report, respond, or orient to sensory or visual stimuli when it appears on the side opposite to the lesion. USN affects motor recovery, functional performance, and quality of life.

Novelty: The proposed study would be the first investigation to utilize the task-based and magnified mirror therapy for both upper and lower limbs and visual feedback by positioning mirror in parasagital position.

Objective: The primary objective is to determine the effectiveness of Task-based and magnified mirror therapy on Unilateral Spatial Neglect (USN) as well as motor recovery among post-stroke hemiparetic subjects.

Methods:

Design: Randomized controlled, single blinded trial

Setting**:** Neuro-Rehab Laboratory

Inclusion criteria: Age: 20 to 80 years, ischemic or hemorrhagic stroke, 1 to 36 months post-stroke, hemiparesis (right or left), USN (an asymmetry between the Letter cancellation task).

Exclusion Criteria: Severe other cognitive impairment, homonymous hemianopia, contractures and deformities of hand / finger, Severe depression.

Sample size: 86

Intervention: Experimental group will receive 40 sessions, 5/week, during 2 months, 1 hour experimental intervention in addition to 1 hour conventional rehabilitation. Experimental intervention will comprise of task-based and magnified mirror therapy for both upper and lower limbs in addition to the visual feedback. Control group will receive dose matched standard rehabilitation only.

Outcome measure: Letter cancellation task, Line bisection test, Fugl-meyer assessment, Catherine Bergego scale, Functional ambulation category, Berg balance scale, Modified Rankin scale.

Data analysis: A repeated-measures 2-way ANOVA will be used to study difference for the post intervention (8-week) and follow-up (4-week) scores between the groups.

Expected outcomes: The proposed study will lead to development of a novel rehabilitation protocol for the management of USN in stroke. The protocol may be favorable in reducing the impact of cognitive disability among post-stroke survivors by reducing USN and enhancing the motor and functional recovery.

1. **Background:**

According to the World Health Organization, more than 15 million people experience stroke worldwide each year. Of these, 5 million die and another 5 million gets permanently disabled.[^1^](#_ENREF_1) 70% of strokes occur in low- or middle-income countries (LMICs) such as India. Consequently, the disability burden in LMICs is greater than that of the high-income countries. Further, it has been projected to cause 23 million first-ever strokes, 77 million stroke survivors, and 61 million DALYs by 2030 in LMICs. Thus, the condition has considerable socioeconomic impact on the patients, family members and health care providers, posing a major public health challenge.[^2^](#_ENREF_2) Presently, the stroke incidence in India is much higher than the western developed countries.[^3^](#_ENREF_3)^,^ [^4^](#_ENREF_4) Stroke incidence ranged from 100 to 150/100,000 every year whereas the prevalence is up to 550/100,000 in various states of India.[^5-8^](#_ENREF_5) Due to upward trend in incidence during the last few decades, the disease has now been considered as an epidemic in India.[^7^](#_ENREF_7)^,^ [^9^](#_ENREF_9) Demographic transitions, longevity, and trends of increasing burden in India call for greater attention to rehabilitation services to improve functional outcomes and quality of life among stroke survivors.

Stroke is the most common cause of cognitive and motor impairments. Among the cognitive deficits include a disorder of spatial awareness known as Unilateral Spatial Neglect (USN). USN is a deficit of attention and is described as the inability to report, respond, or orient to sensory or visual stimuli when it appears on the side opposite to the lesion.[^10^](#_ENREF_10) USN is a disorder which can reduce a person’s ability to look, listen or make movements towards one half of their environment. This can also affect their ability to perform many daily functions, such as eating, reading and dressing. Up to 90% of the post-stroke survivors may experience the spatial neglect.[^11^](#_ENREF_11)

USN is a strong predictor of poor motor recovery and functional performances among the stroke subjects.[^12^](#_ENREF_12) The impaired ability has significant physical, social, and emotional implications. Considering the International Classification of Functioning, Disability and Health, USN undoubtedly affects body structure and function that subsequently leads to activity limitation and participation restriction.

Cognitive rehabilitation has been recommended as one of the important areas of stroke research that warrant independent synthesis of evidence generated in LMICs.[^13^](#_ENREF_13) Further, globally, research on cognitive impairment after stroke is at an earlier stage of evolution than research in motor recovery.[^14^](#_ENREF_14) The studies to enhance cognitive deficits among stroke survivor are recommended as a top first question for research.[^15^](#_ENREF_15) The proposed study may be applicable to the *National Stroke Registry Program (NSRP) / National Programme for Prevention and Control of Cancer, Diabetes, Cardiovascular Diseases and Stroke* (NPCDCS) in terms of rehabilitation services to control and prevent disability for comprehensive management of stroke patients.[^16^](#_ENREF_16)^,^ [^17^](#_ENREF_17)

[^15^](#_ENREF_15)

1. **Literature review:**

USN is a frequent and disabling impairment after stroke. The terms unilateral neglect, visuospatial neglect, hemineglect and spatial neglect are used interchangeably. Although the USN usually occurs on the contralesional side in the right brain damage, the deficit may be observed on the ipsilesional side as well as among subjects with the left brain damage.[^11^](#_ENREF_11)^,^ [^18^](#_ENREF_18)^,^ [^19^](#_ENREF_19) The functional performance of an individual with USN gets hampered. Most of the investigations have been focused on the impairment and management of upper limb functions. In addition to this, the USN affects lower limb functions such as locomotion and stair climbing. The post-stroke subjects with USN are at more risk of falling in comparison to the subjects without USN.[^20^](#_ENREF_20)^,^ [^21^](#_ENREF_21) The functional ambulation including stair climbing gets more impaired than the stroke subjects without USN.[^20^](#_ENREF_20)^,^ [^22^](#_ENREF_22) Further, USN has been identified as a key element that may impede upper limb and lower limb recovery.[^12^](#_ENREF_12)

The management of USN poses challenges in clinical practice, affecting the overall recovery. A wide range of therapeutic approaches has been applied in managing USN, including cognitive, behavioural, and pharmacological therapy.[^23^](#_ENREF_23) However, there is no consensus as to which methods are most effective. Cognitive rehabilitation for USN comprises restitutive and compensatory methods. Techniques using the restitutive approach aim to alter the underlying cognitive impairment. Compensatory techniques include teaching strategies to make behavioural adjustments. The emphasis in compensatory strategies is on coping with and finding ways of adapting to existing impairments. In the recent Cochrane review by *Bowen A et al (2013)*[^11^](#_ENREF_11) it has been concluded that the effectiveness of cognitive rehabilitation interventions for reducing the disabling effects of neglect and increasing independence remains unproven. No cognitive rehabilitation approach can be supported or refuted based on the current evidence. Though no specific technique has been found to be strongly evident for reducing USN, the activity based methods has been recommended to enhance functional performances.[^10^](#_ENREF_10)

Mirror therapy is an evident method for enhancing sensori-motor recovery in poststroke hemiparesis.[^24^](#_ENREF_24) The technique utilizes the mirror-illusion created by the movement of sound limb that is perceived as the paretic limb. The technique is a simple and economical method that can stimulate the brain noninvasively. The intervention unquestionably has neural foundation. Multiple brain areas such as occipital lobe dorsal frontal area, and corpus callosum are involved during the mirror therapy. Bilateral premotor, primary motor cortex, primary somatosensory cortex, and cerebellum reorganize enhancing the function of damaged brain. The motor areas of the lesioned-hemisphere receive visuo-motor processing information through parieto-occipital lobe. Mirror neurons (a set of cells in premotor cortex and inferior parietal lobule activates during observation as well as performing a movement) may also play a possible role in the cortico-mechanism out of mirror therapy.[^25^](#_ENREF_25) The therapy may positively affect body representation in post-stroke subjects with motor impairment. In an investigation carried out by *Tosi G et al (2017)*[*^26^*](#_ENREF_26) on a group of 45 post-stroke patients, following the mirror therapy session bisection scores shifted distally, compatibly with a partial correction of the metric representation of that arm. The effects showed some variability with the laterality of the lesion and the duration of the illness.

*Pandian JD et al (2014)*[*^27^*](#_ENREF_27) in their RCT investigated the effect of mirror therapy on USN among 48 acute (48 hours) post-stroke subjects (thalamic and parietal lobe lesions). The study demonstrated favorable results in favor of mirror therapy (12 hours, 5 days/ week for a month) for reducing USN as measured by star cancellation, line bisection, and picture identification task at 6-month. Only acute stroke, specific area of lesions, and lack of USN-specific functional measure are some of the noticeable weakness of the study. Further, the associated motor recovery was also not considered. In experimental protocol, the subjects were provided only movements as mirror therapy rather than using meaningful tasks as media. *Thieme et al (2012)*[*^28^*](#_ENREF_28) in their RCT among acute stroke (within 3 months) using mirror therapy found positive effect for USN; however, on a small subsample of 3 patients. Other than the small sample, the secondary objective and chronicity are also the major weakness of the study. *Dohle C et al (2009)*[*^29^*](#_ENREF_29)also conducted an RCT using mirror therapy (1/2 hour, 5 days/week for 6 weeks) on 36 acute stroke (within 8 weeks) with middle cerebral artery involvement. In the study, a sub-sample of 20 subjects had USN, the 11 experimental subject exhibited positive effect of mirror therapy. However, the investigator considered the improvement of hemineglect as a positive side effect whose independent therapeutic value remains to be proven. Further studies are recommended to explore the interplay between recovery in the USN and sensori-motor domain.

Mirror has also been recommended to be used a feedback tool among USN subjects. *Ramachndran et al (1999)*[*^30^*](#_ENREF_30) has proposed and tested the position of a mirror on the patient’s right side in the parasagittal plane, so that when the patient rotates his head rightward and looks into the mirror, he sees the neglected side of the world reflected in the mirror. They argued that since the sensory information was coming from the left side, this would make him to overcome the neglect. In their pilot experiments, the presence of the mirror enhanced the patients’ awareness of the neglected field, so that they reached correctly for an object that was shown in the neglected field.

The magnification of vision may increases the cortical representation of the body part. It has been proposed that magnification of a body part might unmask pre-existing connections between cortical areas or disinhibition of pre-existing synapses and the activation of previously silent brain networks.[^31^](#_ENREF_31) *Ambron et al (2018)*[*^32^*](#_ENREF_32) investigated the effect of hand-motor tasks under magnified vision condition on 25 chronic stroke subjects (> 6 months). Twenty-eight percent of individuals showed an immediate significant improvement averaged across all tasks with magnification; similar beneficial responses were also observed in 32% of individuals after a short delay. The results suggested that magnification of the image of the hand may be of utility in rehabilitation of individuals with stroke.

***Rationale:*** Cognitive deficits are a major cause of disability in post- stroke subjects. Spatial neglect has visual, perceptual, and motor factors. Post-stroke with USN exhibited poor functional outcome when compared with individuals without USN. The presence of USN is associated with poor upper limb motor control, both at subacute and chronic stages.[^12^](#_ENREF_12) A range of therapeutic approaches comprising cognitive and behavioral approaches has been applied in visuospatial neglect. However, there is no consensus as to which rehabilitation method is most effective.[^23^](#_ENREF_23) There is very limited evidence that cognitive rehabilitation may have an immediate beneficial effect on neglect. Further, there is a lack of investigations and insufficient evidence related to upper limb therapies in post-stroke subject with USN. This justifies the need for further clinical trials of cognitive rehabilitation for neglect.[^11^](#_ENREF_11) The investigations on USN using mirror therapy have either been conducted on acute subjects or underestimating the importance of motor outcome. The common neurobiological mechanism for proportional recovery rule[^33^](#_ENREF_33) both for the upper limb and USN demands the intervention of dual action. In addition to the upper limb, the USN also affects the motor and functional performance of the lower limb. However, no USN rehabilitation techniques have incorporated the lower limb aspect. The other crucial knowledge gaps in this context are: use of magnified vision for USN and use of mirror in the parasagital plane for USN. It is understood that appropriate and comprehensive intervention for USN would not only reduce the cognitive disability but also induce substantial motor and functional recovery.

1. **Novelty:**

The proposed study would be the first investigation to utilize the tasks for providing the mirror therapy among stroke subjects with USN. The meaningful tasks induce movements that appear out of an interaction between multiple brain areas to manipulate a real-world object. Such movements increase the cortical activity and may reduce greater the deficit than the movements without task.[^34^](#_ENREF_34)

Apart from the upper limb, the activity-based mirror therapy protocol[^35^](#_ENREF_35) will also be provided for the lower limb to comprehensively reduce the impact of USN. This would be the first study to incorporate the lower limbs in any USN rehabilitation study.

Magnifying the image of a body part (hand or arm), has a positive and beneficial effect on activity performance and thus motor recovery among stroke subjects.[^32^](#_ENREF_32)^,^ [^36^](#_ENREF_36) Mirror therapy providing image without magnification has been utilized in management of USN. No cognitive rehabilitation protocol utilizing magnified image of the neglected body part has been investigated yet. The proposed study would be the first investigation of magnified mirror for creating illusion for the affected upper limb by the less-affected side. When the vision of the limb will be magnified, the illusion may induce enlargement of the cortical representation of the body part. Thus, enhancing the underlying neuromechanism[^25^](#_ENREF_25) of mirror therapy.

The fourth novelty of this proposed investigation is the use of mirror therapy to provide visual feedback for the affected limb (upper or lower limb) in the parasagital plane. Although it has been suggested by the developers of the mirror therapy[^30^](#_ENREF_30), no mirror-based rehabilitation trials has applied the concept of visual feedback for USN.

Further, the present study will also be focused on management of USN among chronic stroke[^37^](#_ENREF_37), unlike the previous investigations.

1. **Study objectives**:

**Primary objectives**

- 1. To determine the effectiveness of Task-based and Magnified mirror therapy on Unilateral Spatial Neglect (USN) among post-stroke hemiparetic subjects
  2. To determine the effectiveness of the protocol on motor recovery of the subjects

**Secondary objectives**

- 1. To determine the effectiveness of the Task-based and Magnified mirror therapy on functional performance of the subjects
  2. To determine the effectiveness of the protocol on disability status among the subjects.

1. **Methodology:**

**Hypothesis:**

1. Task-based and Magnified Mirror therapy protocol for the paretic upper limb provided for 2 months will decrease the Unilateral spatial neglect by 50% in 1 to 36 months post stroke subjects with hemiparesis when compared with the conventional management.
2. Task-based and Magnified Mirror therapy protocol for the paretic upper limb provided for 2 months will enhance the motor recovery by 30% in 1 to 36 months post stroke subjects with hemiparesis when compared with the conventional management.

**Design***:* Randomized controlled, single blinded trial

**Setting:** Neuro-Rehab Laboratory*,* Department of Occupational Therapy, Pt. Deendayal Upadhyaya National Institute for Persons with Physical Disabilities, New Delhi

**Inclusion Criteria:**

- Age: 20 to 80 years
- Both male & female
- First episode of unilateral stroke (as defined by WHO)
- Ischemic or hemorrhagic stroke
- 1 to 36 months after the stroke onset
- Hemiparesis (right or left) (as assessed by Fugl-Meyer assessment[^38^](#_ENREF_38) upper extremity subsection: 0 to 66)
- USN (defined as an asymmetry between the Letter cancellation task omissions in the contralesional (left) and ipsilesional (right) visual field of at least 2 letters)[^33^](#_ENREF_33)
- Normal visual abilities (with or without glasses)
- Muscle tone: Modified Ashworth scale 1 to 2

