**Sample size:**

The power calculation was done using the values *(Box 1)* for USN assessment from a study on mirror therapy for USN.[^27^](#_ENREF_27) Considering the beta = 0.1 and α = 0.05, the calculation inferred that 37 subjects in each group would be sufficient to detect the desired change. However, to compensate possible drop outs (15%), 43 subjects in each group will be enrolled. Thus, the total sample size will be **86**.

*Box 1*

| Study | Primary measure | Values used | Alpha | Beta | Estimated sample size each group | Total sample size |
| --- | --- | --- | --- | --- | --- | --- |
| *Pandian JD et al*[*^27^*](#_ENREF_27) | Line Bisection Test | Mean difference = 8.6  SD = 10.6 | 0.05 | 0.1 | 37 | 74 |

**Group Allocation and Concealment:** The subjects will be randomly allocated between the experimental and control groups in block of 10. The assessor will be unaware about the group allocation of the subjects and will apply the outcome measures both pre- and post intervention. The randomization process will be conducted by an office staff, not associated with the study, using the SPSS Version 23 software. The intervention will be allocated in the ratio of 1:1. The assignment will be serially arranged in sealed opaque envelopes. The subjects will also be blinded to the purpose of the experimental intervention.

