**Data Collection:**

The data will be collected using the assessment proforma provided as ***Annexure I.*** The proforma comprises items/questions related to demographic aspects of the subjects such as age, gender, type of stroke, duration of stroke, area of involvement, functional performance. Additionally, the clinical evaluation of a standard neuro-rehabilitation condition will also be covered. All the standardized outcome measures in form of data collecting tool have been provided in the ***Annexure II to VII.***

The flow of study process and schedule of enrolment, intervention, and assessment (SPIRIT guidelines[^55^](#_ENREF_55)) are provided below –

Post- stroke patients (1 to 36 months) – Screened for the eligibility (n=….)

Block Randomization (n=86)

Conventional Rehabilitation –

4 weeks

Experimental intervention (n=43)

(Task-based & Magnified Mirror Therapy) + Conventional Rehabilitation

40 sessions, 2 hours each during 8 weeks

Control Intervention (n=43)

(Conventional Rehabilitation)

Dose matched for duration

40 sessions, 2 hours each during 8 weeks

Enrolment

Allocation

Follow-up

Post intervention Assessment (T2)

Baseline Assessment (T1)

Follow up Assessment (T3)

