**Data Analysis:**

The data will be analyzed by using IBM SPSS version 23.0. The demographic and baseline features of the study participants will be analyzed in form of mean (SD) / median (IQR) / n (%) and appropriate test [(Mann-Whitney U (U) / independent t (t) / chi-square (χ^2^)] tests will be used to analyze the difference for the characteristics between the groups. For inferential statistics, an intention-to-treat analysis method will be used by carrying forward the last observation. A repeated-measures 2-way ANOVA (continuous data; within factor, time; between factor, group) will be used to study difference for the post intervention and follow-up scores between the groups. The pre-intervention score will be considered as the covariate with group as the independent variable and posttest score as the dependent variable. The significance level will be set at *P*<.05. The dummy tables to represent the findings are provided below -

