**Dummy Tables**

**Table 1: Demographic and Clinical characteristics of the participants**

| **S. No.** | **Characteristic** | **Experimental group**  **(n=43)** | **Control group**  **(n=43)** | **Test Statistics** |
| --- | --- | --- | --- | --- |
|  | Age (years) *Mean+SD* |  |  | t:p = |
|  | Time since stroke (months) *Mean+SD* |  |  | t:p = |
|  | Male/female - *n (%)* |  |  | χ^2^:p = |
|  | Socio-economic status (BPL/LIG/MIG/HIG) - *n (%)* |  |  | χ^2^:p = |
|  | Educational qualification (years)  *Mean+SD* |  |  | t:p = |
|  | Marital status (married/unmarried/widowed) - *n (%)* |  |  | χ^2^:p = |
|  | Ischemic/Hemorrhagic - *n (%)* |  |  | χ^2^:p = |
|  | Area of involvement (Frontal/parietal/frontoparietal/internal capsule/ basal ganglia/thalamus/ multiple/others) - *n (%)* |  |  | χ^2^:p = |
|  | Risk factors – *n (%)* |  |  | χ^2^:p = |
|  | 1. Hypertension - *n (%)* 2. Smoking - *n (%)* 3. Alcoholic - *n (%)* 4. Tobacco Use - *n (%)* 5. Hereditary - *n (%)* 6. Diabetes mellitus - *n (%)* 7. Obesity- *n (%)* 8. Pregnancy - *n (%)* 9. Coronary artery disease - *n (%)* 10. Peripheral vascular disease - *n (%)* 11. Dyslipidemia- *n (%)* 12. Previous Stroke - *n (%)* |  |  | χ^2^:p =  χ^2^:p =  χ^2^:p =  χ^2^:p =  χ^2^:p =  χ^2^:p =  χ^2^:p =  χ^2^:p =  χ^2^:p =  χ^2^:p =  χ^2^:p =  χ^2^:p = |
|  | Side of involvement (Right/left) – *n (%)* |  |  | χ^2^:p = |
|  | Dominant side (Right/left) – *n (%)* |  |  | χ^2^:p = |
|  | BRS-U (Stage1/2/3/4/5/6) – *n (%)* |  |  | χ^2^:p = |
|  | BRS-H (Stage 1/2/3/4/5/6) – *n (%)* |  |  | χ^2^:p = |
|  | BRS-L (Stage 1/2/3/4/5/6) – *n (%)* |  |  | χ^2^:p = |
|  | Shoulder subluxation (Grade 1/2/3) – *n (%)* |  |  | χ^2^:p = |
|  | Shoulder support– *n (%)* |  |  | χ^2^:p = |
|  | Hand Splint– *n (%)* |  |  | χ^2^:p = |
|  | MAS (0/1/1+/2) – *n (%)*   1. Shoulder adductors 2. Elbow flexors 3. Forearm pronators 4. Wrist flexors |  |  | χ^2^:p =  χ^2^:p =  χ^2^:p =  χ^2^:p = |
|  | Walking devices (walker/quadripod/stick) – *n (%)* |  |  | χ^2^:p = |
|  | AFO (hinged/non-hinged) – *n (%)* |  |  | χ^2^:p = |
|  | Pain (VAS)   1. Shoulder *(Median; IQR)* 2. Wrist *(Median; IQR)* 3. Hand *(Median; IQR)* |  |  | U:p=  U:p=  U:p= |
|  | Cognitive impairment (mild/moderate) *- n (%)* |  |  | χ^2^:p = |
|  | Psychosocial behavior (depression/aggression) - *n (%)* |  |  | χ^2^:p = |
|  | Speech (Expressive aphasia/dysarthria) - *n (%)* |  |  | χ^2^:p = |

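### Time since stroke spans 1 to 36 months and is recorded, but neither the randomisation nor the outcome model uses it, which gives up some precision and protection against chance imbalance

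*Protocol*

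**What the plan says.** Protocol, Inclusion Criteria: patients may enter "1 to 36 months after the stroke onset".

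Protocol, Group Allocation and Concealment (under Sample size): "The subjects will be randomly allocated between the experimental and control groups in block of 10", and "The intervention will be allocated in the ratio of 1:1". No stratification factor or minimisation is named, and the study flow diagram adds none.

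Protocol, Data Analysis: the model is a two-way repeated-measures ANOVA ("continuous data; within factor, time; between factor, group"). Here time means assessment occasion, not time since stroke. The section continues: "The pre-intervention score will be considered as the covariate with group as the independent variable and posttest score as the dependent variable". No other covariate is named.

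Protocol, Data Collection: the proforma covers "age, gender, type of stroke, duration of stroke, area of involvement, functional performance". Dummy Table 1 has a row beginning "Time since stroke (months", with a t-test between groups. The variable enters no outcome analysis.

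Protocol, Literature review: in describing a mirror-therapy study of 45 post-stroke patients, the Protocol reports that the effects varied with lesion side and with how long the patient had been ill.

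**The concern.** A patient one month after stroke and one three years after it can have the same baseline score and still be expected to change by different amounts over 8 to 12 weeks. The baseline score absorbs part of any such prognostic difference, but it cannot separate those two patients. If time since stroke carries prognostic information beyond the baseline score, leaving it out has two consequences:

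- The residual variance, and so the confidence interval, is wider than it needs to be.
- In a trial of 86, a chance excess of early patients in one arm moves the estimate, and nothing in the plan corrects for it. The t-test in Table 1 describes such a gap but does not adjust for it.

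The Protocol presents the inclusion of chronic patients as a feature that sets it apart from earlier trials, and its own literature review names duration of illness as relevant. Yet its Limitations section lists brain area, type of neglect and motor stage as sources of heterogeneity, and not time since stroke.

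**Working it through.** **Inputs from the Protocol.** Box 1: mean difference 8.6, SD 10.6, alpha 0.05, beta 0.1, 37 per group. Enrolment: 43 per group after 15% dropout.

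**Inputs assumed, because the documents give none.** Share R² of residual variance explained by time since stroke, after the baseline score: 5% to 20%. Share of patients early after stroke: 50%. The SD of 10.6 is taken as the residual SD before this adjustment.

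**1. The plan's own figure.** The two-sided normal formula gives n = 2 × (1.960 + 1.282)² × (10.6/8.6)² = 31.9, so 32 per group (33 with the t distribution). The stated 37 is therefore not reproduced, although 37 × 1.15 = 42.55 does give 43. That is a separate matter. What counts here is that power at 37 per group on these inputs is 93.7%, above the 90% target.

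**2. Gain in precision.** Adjustment multiplies the SD by √(1 − R²) and is equivalent to multiplying the sample size by 1/(1 − R²).

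| R² (assumed) | Fall in standard error | Equivalent extra patients | n per group for 90% power | Power at 37 per group |
| --- | --- | --- | --- | --- |
| none | – | – | 32 | 93.7% |
| 5% | 2.5% | 1/0.95: 5% | 31 | 94.7% |
| 10% | 5.1% | 1/0.90: 11% | 29 | 95.7% |
| 20% | 10.6% | 1/0.80: 25% | 26 | 97.4% |

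**3. Chance imbalance.** With 43 per group, half of all patients early and no stratification, the SD of the between-arm difference in the early share is √(2 × 0.25/43) = 0.108. By the normal approximation, the chance of a gap above 15 percentage points is 2 × [1 − Φ(0.15/0.108)] = 16%. The exact hypergeometric calculation gives 20%.

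**4. What such a gap would do.** A two-category factor split 50/50 with a mean difference of δ SD explains 0.25 × δ² of the variance, so δ = 2√R². A 15-point gap moves the estimate by 0.15 × δ.

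- R² = 10%: δ = 0.63 SD; shift 0.15 × 0.632 = 0.095 SD; × 10.6 = 1.0 units; /8.6 = 12%.
- R² = 20%: δ = 0.89 SD; shift 0.15 × 0.894 = 0.134 SD; × 10.6 = 1.4 units; /8.6 = about 16%.

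The unadjusted standard error of the difference is √(2/43) = 0.216 SD, so these shifts are about 0.4 to 0.6 of a standard error.

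**The case against.** The strongest reply is that nothing here is an error. Randomisation balances time since stroke in expectation, the model already adjusts for the baseline score, and the unadjusted standard error already contains the variability from chance imbalance. The overall 5% error rate therefore holds. This stands. A reader might infer that the wide window biases or confounds the comparison; the documents do not support that.

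Second, the practical gain is small: 1 to 4 points of power in a trial that already exceeds its target on its own inputs. This also stands.

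Third, the Protocol does not show that time since stroke predicts change beyond the baseline score. Its remark about duration of illness concerns variation in the effect of mirror therapy, and a main-effect covariate does not address effect modification. That is fair: the remark makes the variable relevant but does not give its prognostic strength, which is why R² is given as an assumed range.

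Four stronger readings should be resisted.

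- One might assume that early patients recover a full 1 SD more, so that a 15-point gap shifts the result by 0.15 × 10.6 = 1.6 units, or 18% of 8.6. With a 50/50 split that implies 25% of variance explained, beyond the range used for the precision gain.
- One might extend the adjustment to every outcome. Dummy Tables 7 and 8 compare FAC and mRS by chi-square, so there is no model there to take a covariate.
- One might add side of involvement on the strength of the same literature remark. The documents give no basis for the size of its effect on outcome.
- One might say that the plan relies on the Table 1 tests to handle imbalance. Data Analysis uses them only to examine group differences in characteristics.

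Finally, an analysis plan that is not shown might add covariates. However, the Protocol itself fixes the allocation scheme and names one covariate, so the point can be raised against its text.

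**Conclusion.** The point holds as a matter of efficiency and of protection against chance imbalance, not of validity. The Protocol records a plausible prognostic variable over a 35-month range and uses it in neither the allocation nor the model. At 5% to 20% of residual variance explained, adjustment is worth about 5% to 25% more patients, or 1 to 4 points of power. With half the patients early, a gap between arms of more than 15 points has roughly a one in six to one in five chance. At 10% to 20% of variance explained, a 15-point gap would move the estimate by 12% to 16% of the planned difference.

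The R² range and the early share are assumptions. A weaker relation gives a smaller gain, and the case for acting rests on the very low cost. A reader might infer that the mixed population leaves the trial underpowered. That would need 10.6 to understate the SD in this population, because it comes from a trial in acute stroke; the documents give no SD for patients at 1 to 36 months from which to judge this.

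**What to change.** In Data Analysis, after the sentence that names the pre-intervention score as covariate, add time since stroke at enrolment (for example, log months) as a second prespecified covariate in the models for the continuous outcomes: LBT, LCT, FMA, CBS and BBS. Settle its form before any outcome data are seen by group. The cost is one line of text and one degree of freedom for the group comparison; the variable is already on the proforma.

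If the randomisation list has not been made, the blocks could also be stratified by early versus late after stroke, at a cut that the investigators fix in advance. This is optional, and the covariate is worth having either way.

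FAC and mRS are outside this change. Adjusting them would mean replacing the chi-square comparisons with a different model, which is a separate decision.
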